### Evaluation criteria and efficacy judgment

2.7

(1)Total effective rate: refer to the clinical efficacy evaluation standard of Chinese Ophthalmology Clinical efficacy Diagnostic Standard.^[12]^ Obvious effect: Microaneurysms and other symptoms all or most disappeared, visual acuity improved more than 3 lines, visual field expanded 10 to 15 degrees or more; Effective: Microaneurysms and other symptoms significantly relieved, visual acuity improved more than 2 lines, visual field expanded 5 to 10 degrees or more; Ineffective: the above standard are not met or symptoms are aggravated. Total effective rate = (significant number + effective number)/total number∗ 100%.(2)The BCVA and central macular thickness before and after treatment, BCVA examination will be performed using a standard logarithmic acuity chart, and the results are converted LogMAR recording method, and the central macular thickness is measured using optical coherence tomography.(3)Adverse reactions: nausea, dizziness, rash, visual functional damage, and other discomforts occurred during the treatment.

### Data collection and management

2.8

All patients are followed up for 12 months after treatment, and the visual acuity and curative effect are evaluated with the same equipment and method before treatment at 1 day, 1 months, 3 months, 6 months and 12 months after treatment. The whole process of data collection and recording is carried out by 1 or 2 assistants. Personal information about potential participants and registered participants will be collected, shared and stored in a separate storeroom to protect pre-trial, in-trial, and post-trial confidentiality. The access to the database will be restricted to the researchers in this study team.

### Statistical analysis

2.9

The collected data are analyzed by SPSS 18.0 software. A chi-square test is used for counting data, mean ± standard deviation ($\bar{x}\pm s$) is used for measurement data, independent sample *t* test is used for normal distribution. Mann-Whitney *U* test is used for skewed distribution. When *P* *<* .05, and the difference is considered to be statistically significant.

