### Sample size

2.3

The calculation of sample size is based on the mean and standard deviation of best corrected visual aculty (BCVA) at 3 months after surgery. According to the results of the pilot study, the experimental group is 0.37 ± 0. 14, and the control group is 0.44 ± 0.13. Set α = 0.025, 1 sided test, β = 0.20. Calculated by the PASS15.0 software, each group needs 60 participants, with an estimated withdrawal rate of 10%, and each group will include 67 participants.

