### Study design

2.5

Eligible participants are randomly assigned to either the treatment group or the control group in a 1:1 ratio using a random tool based on a central network. The random sequence randomization is performed without any stratification by independent statisticians who do not participate in the implementation of the experiment or statistical analysis using SAS 9.3 software (SAS Institute, Cary, NC). The clinical research coordinator enters participant information on the tablet and is given a random number. The research assistant gets the allocation of participants from the computer. Throughout the study, the research assistant is responsible for screening, recruiting participants, and assigning random numbers to participants who have been included. Results the evaluator is responsible for the evaluation of the scale. Considering the actual operational nature of acupuncture, participants and practitioners may be aware of random distribution. However, the evaluators of research results and the statisticians of data statistics and analysis are not informed of the distribution situation.

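### Continuous outcomes are tested without their measured baseline: the stated tests are valid, but they give up precision that ANCOVA would recover at no cost

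*Protocol article*

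**What the plan says.** Section 2.9 (Statistical analysis) sets the analysis of continuous outcomes by distribution: an "independent sample *t* test is used for normal distribution", and a Mann-Whitney U test if the data are skewed. It mentions no covariate, change score or repeated-measures model.

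Section 2.7 lists as outcomes "The BCVA and central macular thickness before and after treatment", with acuity recorded as logMAR and thickness taken from optical coherence tomography. Section 2.8 places a visual acuity assessment before treatment and further ones at 1 day and 1, 3, 6 and 12 months after it. A baseline value is therefore planned for every participant.

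On allocation, section 2.5 states: "The random sequence randomization is performed without any stratification". The ratio is 1:1.

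Section 2.3 sizes the trial on follow-up values, "based on the mean and standard deviation of best corrected visual aculty (BCVA) at 3 months after surgery". The pilot figures are: "the experimental group is 0.37 ± 0. 14, and the control group is 0.44 ± 0.13". The error rates are: "Set α = 0.025, 1 sided test, β = 0.20". The result is that "each group needs 60 participants, with an estimated withdrawal rate of 10%, and each group will include 67 participants".

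**The concern.** A baseline measurement of the same quantity usually explains part of the variation in the follow-up measurement. A two-sample test that ignores it leaves that variation in the standard error. The confidence interval is then wider and the power lower than the collected data allow. Unstratified allocation also means that the design does not hold baseline acuity or thickness balanced between arms, so part of any chance imbalance carries into the unadjusted contrast.

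A smaller, related point is that the observed distribution decides between a comparison of means and a comparison of ranks. The quantity being tested could then differ between outcomes or visits, whereas section 2.3 sizes the trial on a difference in means.

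At stake is the precision of the main visual acuity comparison in a trial planned at only 80% power.

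**Working it through.** **Inputs from section 2.3.** Means 0.37 and 0.44, so the difference is 0.07. SDs 0.14 and 0.13. One-sided alpha 0.025, power 0.80, withdrawal 10%. Allocation 1:1 (section 2.5).

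**Assumed, not in the protocol.** The correlation rho between baseline and 3-month BCVA, shown at 0.3, 0.5 and 0.7. A baseline SD equal to the follow-up SD (about 0.135), needed for the change-score and imbalance figures.

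**Step 1: reproduce the plan's figure.**
- Pooled SD = sqrt((0.14² + 0.13²)/2) = 0.1351. Standardised difference = 0.07/0.1351 = 0.518.
- Normal approximation: n = 2 × (1.960 + 0.842)² × 0.1351²/0.07² = 58.5, so 59 per group.
- Noncentral t: power is 0.797 at 59 and 0.804 at 60, so 60 per group.
- Withdrawal: 60/0.90 = 66.7, so 67 per group.

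The stated 60 and 67 are right for an unadjusted t test on 3-month values.

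**Step 2: add the baseline as covariate.** ANCOVA reduces the residual SD to SD × sqrt(1 − rho²). Power is for 60 per group at one-sided 0.025 (noncentral t, one degree of freedom spent on the covariate).

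| rho (assumed) | Variance factor 1 − rho² | Fall in SE, 1 − sqrt(1 − rho²) | Power, unadjusted | Power, ANCOVA |
|---|---|---|---|---|
| 0.3 | 0.91 | 5% | 0.804 | 0.839 |
| 0.5 | 0.75 | 13% | 0.804 | 0.902 |
| 0.7 | 0.51 | 29% | 0.804 | 0.976 |

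The unadjusted test gives up about 3.5, 10 and 17 percentage points of power.

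**Step 3: if change from baseline is what is tested.** The SD of change is SD × sqrt(2(1 − rho)): 0.160, 0.135 and 0.105. Power at 60 per group is 0.66, 0.80 and 0.95. This is below ANCOVA at each rho, and at rho 0.3 it is well below the unadjusted test of follow-up values.

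**Step 4: chance imbalance.** The SE of the baseline difference is 0.1351 × sqrt(2/60) = 0.0247 logMAR. A baseline difference of size b shifts the expected follow-up contrast by about rho × b. For b = 0.035 (half the target difference) the shift is 0.3 × 0.035 = 0.011, 0.5 × 0.035 = 0.018 or 0.7 × 0.035 = 0.025.

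For the follow-up contrast itself to move by 0.035 through this route, b must reach 0.035/rho = 0.117, 0.070 or 0.050. These are 4.7, 2.8 and 2.0 SEs, with two-sided probabilities below 0.001%, about 0.5% and about 4%.

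**Step 5: macular thickness.** The protocol gives no SD for it, so only the variance factor 1 − rho² can be stated.

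**The case against.** The best defence is that nothing here is an error. Under randomisation the unadjusted t test keeps its type I error and is unbiased on average, and its standard error already allows for chance baseline imbalance. The sample size was computed for that test and reproduces, so sections 2.3 and 2.9 agree. All of this stands.

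Section 2.9 also does not say whether follow-up values or changes are tested, and the before-and-after wording in section 2.7 would fit change. This stands too. The 3-month means in section 2.3 point to follow-up values, and Step 3 shows that ANCOVA is ahead under either reading.

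The gain depends on a correlation that the protocol does not give, and it is small near 0.3. This stands as a limit on the size of the point.

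Covariates are often left to an analysis plan that is not shown here. That carries less weight, because section 2.9 names the tests. How normality would be judged is closer to detail that such a plan could hold, so the switching between tests is secondary.

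A reader might infer two stronger claims. The first is that a chance baseline difference enters the result in full, so that the roughly 16% chance of a baseline difference above 0.035 is the chance of a distortion of half the target effect. Step 4 shows otherwise: only about rho times the imbalance carries over. The second is that retinopathy stage or baseline acuity is a dominant predictor that the design neglects. The protocol says nothing on their prognostic strength, and unstratified 1:1 randomisation is a legitimate design.

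**Conclusion.** The point holds as one of efficiency and precision, not of validity. The planned test delivers its planned 80% power. Using the baseline that is already being collected would raise this to between 84% and 98% for assumed correlations of 0.3 to 0.7, with a standard error 5% to 29% smaller. The figures rest on the pilot means and SDs, 60 analysed per group and the assumed correlation. They apply to 3-month BCVA only. For macular thickness the direction is the same, but its size cannot be given. The change is worth making because it is nearly free. The documents do not support calling the present analysis biased or the sample size wrong.

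**What to change.** In section 2.9, prespecify an ANCOVA of logMAR BCVA at 3 months, the visit used for sizing, on treatment arm and baseline BCVA. Report the adjusted mean difference with its 95% confidence interval. Analyse central macular thickness in the same way with its own baseline. Retinopathy stage may be added as an optional further covariate if it is named in advance. Keep Mann-Whitney as a sensitivity analysis, so that the observed distribution does not choose the main test. The sample size can stay as it is.

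The cost is one paragraph of wording, fixed before the data are examined. It needs no extra participants, visits or measurements, and SPSS can fit the model.

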## Discussion

3

Diabetic retinopathy is an eye disease with specific changes in diabetes, and it is 1 of the most common and serious microvascular complications of diabetes.^[13]^ The main pathological changes in DR are ischemia and hypoxia in local retina, loss of fundus pericytes, disturbance of ocular vascular microcirculation, changes in the vascular wall and hemorheology, and finally induce neovascularization.^[3,14]^ At present, clinical treatment of DR mainly includes retinal laser photocoagulation, vitrectomy, anti-vascular endothelial growth factor drugs and so on, but the therapeutic effect is not ideal.^[2,15]^

Qiming granule is the first proprietary Chinese medicine approved by National Medical Products Administration for the treatment of DR. It is composed of Radix Astragali, Radix Puerariae, Radix Rehmanniae, Fructus Lycii, semen Cassiae, Fructus Rehmanniae, Radix Puhuang and Leech.^[16]^ Qiming granule has the effects of benefiting Qi, nourishing the liver and kidney, dredging collateral and clear eyes, enhancing immune function, promoting cell growth, improving microcirculation, lowering blood sugar and lipid. It has become 1 of the most widely used proprietary Chinese medicines in the treatment of DR in China.^[17]^ Animal experimental studies have found that qiming granule can reduce the level of blood glucose in rats, reduce the degree of retinal angiopathy, reduce the thickness of retinal capillary basement membrane,^[18]^ and inhibit retinal neovascularization by inhibiting inflammatory response and oxidative stress in DR rats.^[19]^

PRP is an effective method for the treatment of DR, which can reduce the release of neovascularization factors induced by ischemia and hypoxia and delay the progression of the disease.^[4]^ However, because PRP destroys the retinal photoreceptor retinal pigment epithelial complex, macular edema, visual function damage, visual field defect and other side effects will occur.^[5,20]^ There is evidence that qiming granule combined with fundus laser can promote macular edema absorption, reduce leakage, improve visual acuity and improve the total effective rate of treatment.^[21]^ Since there is no standard clinical study to evaluate the efficacy of qiming granule combined with laser in the treatment of diabetic retinopathy, we intend to evaluate its efficacy and safety through prospective RCTs.

This study also has some limitations: This study is a single-center randomized controlled study. The included population is regional, which may affect the results. At the same time, due to the influence of treatment, this study can not achieve strict double-blind, may have a certain impact on the results.
